### Outcome measures and data collection

The list of data collection instruments and time of data collection are presented in Table 3 and Fig. 3. The primary outcome of this study is the measurement of female SF during pregnancy and at 3 months postpartum which will be assessed using the Female Sexual Function Index (FSFI) [42]. The FSFI is a valid and reliable [42] multidimensional self-reported instrument for the assessment of female SF. It consists of 19 questions grouped into six domains: desire, arousal, lubrication, orgasm, satisfaction and pain. A value of 0–5 is attributed to each answer. The scores range from 2 to 36 and the lower the score, the worse the SF [42]. There are cut-off points to predict female sexual dysfunction. In 2006, Weig et al. [1] validated the FSFI in the USA and found that a cut-off score of 26.55 was enough to classify 70% of women with sexual dysfunction in the normal population. This score cannot be used for specific groups such as pregnant women, postpartum women, menopausal women and so forth [1]. SF will be assessed at 20 and 36 weeks’ gestation and at 3 months following birth.

**Table 3 Tab3:** Data collection instruments and time of data collection

	Collection time							
	Booking		36 weeks’ gestation		Birth		3 months after birth	
Data and tools	CG	IG	CG	IG	CG	IG	CG	IG
Primary outcomes								
SF (FSFI)	√	√	√	√	–	–	√	√
Secondary outcomes								
Urinary incontinence (UDI-6)	√	√	√	√	–	–	√	√
Faecal incontinence (FI questionnaire)	√	√	√	√	–	–	√	√
Specific quality of life (IIQ-7)	√	√	√	√	–	–	√	√
Childbirth outcomes (Obstetrix Database)	–	–	–	–	√	√	–	–
Confounding variables								
Depression (EPDS)	√	√	–	–	–	–	√	√
Relationship (RAS)	√	√	–	–	–	–	√	√
Expectancy questionnaire	√	√	–	–	–	–	–	–
Baseline data (Obstetrix Database)	√	√	–	–	–	–	–	–
Antenatal history (Obstetrix Database and survey)	√	√	√	√	–	–	–	–
Postpartum history (Obstetrix Database and survey)	–	–	–	–	–	–	√	√

*CG* control group, *IG* intervention group, *SF* sexual function, *FSFI* Female Sexual Function Index, *UDI-6* Urinary Distress Inventory, *FI* Waxner short form of faecal incontinence, *IIQ-7* Incontinence Impact Questionnaire, *EPDS* Edinburgh Depression Scale, *RAS* Relationship Assessment Scale

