### Sample size

The sample size of this study was calculated based on the recent research available on the impact of PFME on SF in the postpartum period. Using information from this study [52], a total FSFI score of 28.9 ± 4.54 in the intervention group after PFME and 26.6 ± 4.40 in the control group and a standard deviation of 4.54 in both groups, a sample size of minimum of 62 in each arm would be required to detect a 9% difference in FSFI scores between groups (80% power and *α* = 0.50). The treatment and control ratio is 1. Allowing for 20% attrition during pregnancy, around 160 women are needed to be recruited. However, considering the possibility of a higher rate of withdrawal at 3 months after birth and anticipating 30% attrition after birth, 200 women will be randomised.

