### Statistical analysis

Analysis of the primary and secondary outcomes will be based on an intention-to-treat basis, which will include withdrawal and losses to follow up. Descriptive statistics including numbers and proportions, and means and standard deviations will be used. Primary analysis including chi-square and Student’s *t* tests will be used to examine group differences in the primary and secondary outcomes. Repeated ANOVA will be used in order to assess within-patient correlation. Effect sizes will be reported with 95% confidence intervals, and results will be considered significant if *P* < 0.05. Data will be analysed using SPSS.

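### FSFI is primary at both 36 weeks and 3 months postpartum, each judged at a flat P < 0.05 with no rule for combining them, while the sample size covers one comparison

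*Protocol article*

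**What the plan says.** Under Outcome measures and data collection, the protocol article says: "The primary outcome of this study is the measurement of female SF during pregnancy and at 3 months postpartum". The timing follows in the same section: "SF will be assessed at 20 and 36 weeks’ gestation and at 3 months following birth". Table 3 lists the FSFI under primary outcomes at booking, 36 weeks and 3 months after birth. The booking value is a baseline, so two primary time points remain after randomisation.

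The Statistical analysis section says: "Primary analysis including chi-square and Student’s *t* tests will be used to examine group differences in the primary and secondary outcomes". It adds: "Repeated ANOVA will be used in order to assess within-patient correlation". It closes with one criterion: "results will be considered significant if *P* < 0.05". The article does not rank the time points, divide alpha between them or say that both must succeed.

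The Sample size section describes a calculation "based on the recent research available on the impact of PFME on SF in the postpartum period". It uses "a total FSFI score of 28.9 ± 4.54 in the intervention group after PFME and 26.6 ± 4.40 in the control group", with a common SD of 4.54 and 80% power, and arrives at a minimum of 62 per arm for one between-group comparison. It allows for 20% attrition in pregnancy and 30% after birth, and 200 women are to be randomised.

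**The concern.** With two primary time points and one unadjusted threshold, a significant result at either visit could be reported as the trial's primary finding. The nominal 5% would then apply to each test, not to the primary claim. The sample size gives no help, because it was set for one comparison.

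The two visits could plausibly disagree. The exercise programme runs until birth, and the Discussion says that the fortnightly follow-up stops at birth. An effect could be present at 36 weeks and gone by 3 months, or the reverse. The article gives no basis for calling the trial positive or negative in that case.

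**Working it through.** **Inputs.** From Sample size: means 28.9 and 26.6, SD 4.54, power 80%, ratio 1:1, attrition 20% in pregnancy and 30% after birth, 200 randomised. From Statistical analysis: threshold 0.05. Assumed: two-sided tests, attrition counted from randomisation, and a correlation ρ between the two test statistics, for which the article gives no figure.

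**1. Reproduce the plan's figure.** The difference is 28.9 − 26.6 = 2.3, and the standardised difference is 2.3/4.54 = 0.507. With n per arm = 2(z₀.₉₇₅ + z₀.₈₀)²/0.507², the result is 61.2, rounded up to 62. The t-based solution is 62.1. The stated 62 is therefore one two-sided test at 0.05, with no allowance for a second. (The Sample size section prints α as 0.50, which would give 18 per arm two-sided. That is a separate point; only 0.05 reproduces 62.)

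**2. Women expected at each visit.** At 36 weeks: 200 × 0.8 = 160, or 80 per arm. At 3 months: 200 × 0.7 = 140, or 70 per arm.

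**3. False-positive rate if either visit suffices.** Under no effect at either time, the rate is 1 − P(|Z₁| < 1.96 and |Z₂| < 1.96), with Z₁ and Z₂ bivariate normal with correlation ρ. At ρ = 0 this is 1 − 0.95² = 9.75%.

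| Assumed ρ | Either visit significant |
|---|---|
| 0 | 9.75% |
| 0.3 | 9.5% |
| 0.5 | 9.1% |
| 0.7 | 8.3% |
| 0.9 | 7.0% |

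Every value is above 5%. If both visits had to be significant, the rate would be at most 5%.

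**4. Power under two remedies (t-based, difference 2.3, SD 4.54).**

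| Remedy | 3 months, 70 per arm | 36 weeks, 80 per arm |
|---|---|---|
| 3 months as single primary, tested first at 0.05 | 84.5% | tested only if 3 months is significant |
| Alpha split, 0.025 each | 76.7% | 82.6% |

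At 0.025 the t-based requirement is 75.3, so 76 per arm. Allowing for 30% attrition, that is 152/0.7 = 217.1, or 218 women, more than the planned 200.

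**The case against.** **The error rate is conditional.** The article does not say that a t test is run separately at each visit, or that success at one visit is enough. It joins the two periods with a plain 'and', and it also names a repeated-measures ANOVA. A reader might infer that the type I error is definitely above 5%, or definitely 9%. The text does not support that: a both-must-win reading would keep it at or below 5%, and 9.1% needs a correlation near 0.5 that is not given. This part of the objection stands, and the figure is worded accordingly. It does not remove the defect, because the text as written permits the either-visit claim.

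**Several types of test.** A reader might infer that chi-square, t test and ANOVA all count towards the primary claim and raise the error further. In a null simulation with ρ from 0.3 to 0.7, counting such extra tests gave roughly 12% to 19%, depending on which were included. The article does not say they count. Its sentence on tests pools primary and secondary outcomes, and the secondary list contains categorical items (mode of birth, episiotomy, perineal trauma, fetal presentation) for which chi-square is natural. The ANOVA's only stated purpose is within-patient correlation.

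**Chi-square on FSFI.** A reader might see a contradiction between the chi-square test and the remark about the 26.55 cut-off: "This score cannot be used for specific groups such as pregnant women, postpartum women, menopausal women and so forth". No dichotomised FSFI is planned anywhere, so there is none. The remark also rejects only that cut-off; it does not say that no valid cut-off exists for these women.

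**A condensed article, with an analysis plan not shown.** Alpha handling is often left to the analysis plan, and such a plan may hold a rule. The point rests on what the article does state: two primary time points and an unqualified threshold. A later rule would have to narrow that wording.

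**Choice of remedy.** The study aim covers pregnancy and the first 3 months alike, so putting 3 months first is a choice. Splitting alpha, requiring both, or a single repeated-measures test would also close the gap.

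**Conclusion.** The concern holds in this form: the article names two primary FSFI time points, sets a flat 0.05 threshold, and gives no order, split or joint rule, while the sample size supports one two-sided comparison at 0.05 based on postpartum data. If each visit has its own t test and either can carry the claim, the false-positive rate is about 7% to 9.75% for assumed correlations from 0.9 down to 0. The excess over 5% comes from the two time points alone. It does not depend on the number of test types, and nothing here shows that chi-square is misapplied to the FSFI.

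**What to change.** Name the between-group difference in mean FSFI total score at 3 months postpartum as the single primary endpoint. This matches the study from which the sample size was derived and keeps 84.5% power with 70 women per arm. Test FSFI at 36 weeks second, at 0.05, only if the 3-month test is significant. Otherwise report the 36-week difference as an estimate with its 95% confidence interval. As a clarification, add that chi-square applies to categorical outcomes and not to the FSFI.

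The cost is wording in the protocol, the registry entry and any analysis plan. It needs no extra participants, but it should be settled before outcome data are analysed by group. The real downside is that no confirmatory claim about pregnancy is possible if the 3-month test fails, which matters because the aim covers both periods. If the investigators want both times to stand on their own, 0.025 at each controls the error but leaves the 3-month comparison at about 76.7% power, below the planned 80%, unless more women are randomised.

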**Fig. 3 Fig3:**
[figure not shown]
The schedual of enrollment, interventions and assessment

The secondary outcome endpoints will be examined as follows:Childbirth outcomes will include duration of the first, second and third stages of labour, fetal positions and presentation at birth; mode of birth; episiotomy and perineal trauma (1st, 2nd, 3rd and 4th degree perineal lacerations); and fetal outcomes including the APGAR score, head circumference, length and weight. Data regarding childbirth outcomes and fetal outcomes will be obtained from the hospital database after birth.Urinary incontinence symptoms and specific quality-of-life measures will be assessed using the short forms of the Urogenital Distress Inventory (UDI-6) [43] and the Incontinence Impact Questionnaire (IIQ-7) [43] at the time of booking at 20 weeks’ gestation, at 36 weeks’ gestation and also at 3 months following birth. The short forms of the UDI-6 and IIQ-7 are composed of six and seven questions, respectively. They are validated self-report questionnaires and have been shown to have a high degree of correlation with the longer forms of these questionnaires. Both questionnaires are recommended by the second international consultation on incontinence [44]. The UDI-6 is a six-item symptom inventory, specific to symptoms associated with lower urinary tract dysfunction, and combines information on stress, obstructive and discomfort symptoms. The IIQ-7 is a seven-item life-impact assessment instrument specific to UI, and covers separate domains of physical activity, travel, social/relationships and emotional health. Both measures were developed for self-administration and are intended to be used in combination. Women rate how much they experience impaired function of UI and the extent to which this UI affects their daily functioning with four response options per item (0 = “not at all”; 1 = “slightly”; 2 = “moderately”; 3 = “greatly”). For this study, we maintained the scoring procedure as described by the original developer: if more than two items are missing, a total score is not to be calculated. The mean score of items is multiplied by $$ 33\raisebox{1ex}{$1$}\!\left/ \!\raisebox{-1ex}{$3$}\right. $$ to convert to a 0–100 scale. Higher scores indicate more symptom distress (UDI-6) or more impact on daily life (IIQ-7) [45].Faecal incontinence (FI) symptoms will be assessed using a Waxner short form of faecal incontinence questionnaire [46] and has been validated in Australia [47]. The Waxner classification is a 20-point scale used to determine the severity of faecal incontinence and is widely used in Europe [46]. The Waxner questionnaire consists of five questions addressing solid, liquid, gas, changing underwear and lifestyle. Excellent or a score of 0 means continent to liquid and solid stool. Fair means incontinent to liquid and flatus. Poor or a score of 20 means total incontinence [46].

In order to examine the baseline characteristics that might interfere with the effect of PFME on SF, women in both control and intervention groups will be asked about depression symptoms (using the Edinburgh Postnatal Depression Scale (EPDS) questionnaire) [48]. The 10-question EPDS is a valuable and efficient way of identifying patients at risk for “perinatal” depression. Scores above 12 require further assessment and appropriate management as the likelihood of depression is high. Any woman who scores 1, 2 or 3 on item 10 requires further evaluation before leaving the office to ensure her own safety and that of her baby [48].

The other factor that can interfere with the effect of PFME on SF is the relationship with the partner. In this study, a relationship questionnaire [49] will be used at the time of enrolment and at 3 months following birth. The Relationship Assessment Scale (RAS) used in this study consists of seven questions. Scores could range from 1 (low satisfaction) to 5 (high satisfaction). The scores are added up and divided by 7 to get a mean score. The RAS is internally consistent and is solidly and consistently related to measures of relevant constructs such as love and self-esteem [49].

Women in the intervention group will also be provided with the expectancy questionnaire [50] at the time of enrolment. As there is no standard expectancy questionnaire available, for the purpose of this study a questionnaire was designed based on a questionnaire extracted from a study by Devilly and Borkovec [50]. This questionnaire will provide information on women’s expectation of treatment. Belief usually has two aspects to it: (1) what one thinks will happen; and (2) what one feels will happen. The original questionnaire has demonstrated high internal consistency within each factor and good test–retest reliability [50].

Data to be collected from the woman at baseline include: age, gestational age, education, economic status, country of birth, relationship status, smoking habits, remedies or medication history, medical, surgical and psychological history (such as mental illness or depression), family history including domestic violence and alcohol and drug abuse. Antenatal, birth and postpartum history will be obtained from the hospital database and a self-designed survey. The survey will be completed at the time that questionnaires are given to women at the time of booking, at 36 weeks’ gestation, and at 3 months after birth.

To assess the compliance rate, women will be given a diary to record their PFME daily. These data will be collected and recorded monthly by the researcher.

All questionnaires are self-report questionnaires and will be delivered electronically through the REDCap electronic system [51] to women unless they choose to receive hardcopies. The first researcher ([name]) will collect the data. All missing data will be reported with reasons given and patterns of occurrence explored. If women withdraw from the study, no more additional information will be collected; however, the personal information already collected will be retained to ensure that the results of the research project can be measured properly and to comply with the law.

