The pelvic floor is a rich and dynamic system of interconnected muscles, nerves and ligaments that play a major role in maintaining urinary continence in childbearing women. During birth, the baby’s head stretches the surrounding structures and this stretching may result in damage to the muscles, nerves and connective tissues of the pelvic floor. An association between childbirth and urinary incontinence (UI) may be exacerbated by the use of forceps and can lead to long-term pelvic floor muscle dysfunction and urinary or faecal incontinence [19–21]. PFME before the labour and birth could produce strong and well-controlled muscles, reducing incontinence and even potentially reducing fatal malposition and malpresentation [22, 23]. Studies that examined the effect of PFME on labour show mixed results. There are studies demonstrating that women randomised to antenatal PFME had a lower rate of prolonged second stage of labour, less breech presentations and a lower episiotomy rate. The authors concluded that PFME appeared to facilitate rather than obstruct labour [23]. However, another study found no effect of PFME on the duration of the second stage of labour or the rate of instrumental birth [24]. There is additional evidence that PFME may have an effect on reducing faecal incontinence particularly at 1 year postpartum [25].

Therefore, a pragmatic parallel, randomised controlled trial was designed to investigate the effect of antenatal PFME on SF during pregnancy and the first 3 months following birth. The secondary objectives of this study are to investigate the effect of PFME on childbirth outcomes, urinary and faecal incontinence symptoms and specific quality-of-life measures during pregnancy and the first 3 months following birth.

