### Eligibility criteria

Low-risk primiparous women who present to the antenatal clinic for antenatal care will be approached to participate in the study. Women will be eligible if they are primiparous, over 18 years old, ≤ 22 weeks’ gestation, have a singleton pregnancy, anticipating a vaginal birth and have no history of urinary incontinence, pelvic surgery or pelvic organ prolapse at baseline. They also should have no previous history of depression, mental illness, alcohol and drug use or domestic violence and they need to be able to read, understand and communicate in English. Participants in the treatment group must also agree not to perform a PFME programme other than that provided in this study. Women will be excluded if they are over 22 weeks’ gestation, planning to give birth via caesarean section at the time of booking, multiparous, have a multiple pregnancy, have complicated pregnancies (type 1 and type 2 diabetic, vaginal bleeding, baby with abnormalities, etc.) and have known pelvic floor muscle dysfunction. Women who are not able to read and understand English to answer the questionnaires will also be excluded from this study.

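### Labour-stage durations cannot be compared by intention to treat, because women delivered by caesarean lack them and mode of birth is itself an outcome the exercise may affect

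*Protocol article*

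**What the plan says.** The childbirth outcomes in Outcome measures and data collection include "duration of the first, second and third stages of labour" and, in the same list, "mode of birth; episiotomy and perineal trauma (1st, 2nd, 3rd and 4th degree perineal lacerations". They stand side by side as secondary outcomes, all taken from the hospital database after birth.

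Eligibility criteria require women to be "anticipating a vaginal birth" and exclude those "planning to give birth via caesarean section at the time of booking". Booking is at less than 22 weeks. Nothing removes a woman whose caesarean is decided later in pregnancy or during labour.

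The Background offers a route by which PFME might influence mode of birth, "even potentially reducing fatal malposition and malpresentation" (the first adjective is evidently a slip for fetal). It also cites trials with a "lower rate of prolonged second stage of labour, less breech presentations and a lower episiotomy rate". It calls the evidence on labour mixed and reports another study that found no effect on second-stage duration or instrumental birth.

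Statistical analysis states: "Analysis of the primary and secondary outcomes will be based on an intention-to-treat basis, which will include withdrawal and losses to follow up". It names chi-square and Student's t tests for group differences in the primary and secondary outcomes and makes no exception for childbirth outcomes.

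**The concern.** A woman delivered by caesarean before full dilatation has no second stage. One delivered by caesarean during the second stage has a duration cut short by the operation, and the first stage can likewise be absent or truncated. These values are not lost to follow-up; they do not exist as measures of a completed stage. A t test of second-stage duration therefore uses only women who reached, or completed, that stage. That subset is formed after randomisation by mode of birth, which the plan lists as an outcome in its own right.

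If PFME changes who has a caesarean, the two arms' subsets are no longer comparable. Suppose it averts caesareans in women whose labours tend to be long. Those women then enter the PFME arm's average while their counterparts stay out of the control arm's, and PFME could appear to lengthen labour although no woman's labour was lengthened. A rise in caesareans would mislead in the other direction. The effect of PFME on childbirth outcomes is a stated secondary objective, so this bears on what the trial may conclude there.

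**Working it through.** **Plan's own figure.** The plan gives no rate, effect or sample size for any childbirth outcome, so there is nothing to reproduce on this point. Its one calculation concerns the Female Sexual Function Index: 2 × (1.960 + 0.842)² × 4.54² / 2.3² = 61.2, hence 62 per arm at two-sided 0.05, as stated. The argument below does not depend on it.

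**Can the statements all hold?**
- Every secondary outcome is analysed by intention to treat (Statistical analysis).
- Stage durations are secondary outcomes (Outcome measures and data collection).
- Caesarean after randomisation remains possible (Eligibility criteria).
- A woman with a caesarean before the second stage has no second-stage duration.

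The first statement cannot be met for stage durations.

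**Size of the possible bias.** From the plan: 200 women at 1:1, so 100 per arm. Assumed, because the documents give no figures: caesarean rates of 15% to 35%, and a correlation ρ of 0.3 to 0.7 between a normally distributed liability to caesarean and standardised second-stage duration. PFME is given no effect on any woman's duration. Women above the liability threshold have a caesarean and drop out of the comparison.

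With caesarean rate c and z the (1 − c) normal quantile, the mean duration among vaginal births is −ρλ(c), where λ(c) = φ(z)/(1 − c):
- λ(0.15) = 0.233/0.85 = 0.274
- λ(0.20) = 0.280/0.80 = 0.350
- λ(0.25) = 0.318/0.75 = 0.424
- λ(0.35) = 0.370/0.65 = 0.570

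The bias, PFME minus control, is ρ × [λ(control rate) − λ(PFME rate)]. For 25% against 20% it is 0.3 × 0.074 = 0.022 up to 0.7 × 0.074 = 0.052. A simulation of 2,000,000 women agrees to within about 0.001 SD. The false-positive rate is Φ(−1.96 + δ) + Φ(−1.96 − δ), where δ is the bias divided by its standard error with 100(1 − c) women per arm.

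| Caesarean, control vs PFME | Bias in SD (ρ = 0.3 / 0.5 / 0.7) | False-positive rate |
|---|---|---|
| 25% vs 25% | 0 / 0 / 0 | 5.0% |
| 25% vs 20% | 0.022 / 0.037 / 0.052 | 5.2% / 5.7% / 6.5% |
| 25% vs 15% | 0.045 / 0.075 / 0.104 | 6.0% / 7.9% / 11.6% |
| 35% vs 25% | 0.044 / 0.073 / 0.103 | 5.8% / 7.5% / 10.9% |

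**The mechanism in round numbers (all assumed).** Take 70 vaginal births per 100 in control, with a mean second stage of 60 min. PFME averts 10 caesareans, and those ten women have second stages of 120 min. The PFME mean is (70 × 60 + 10 × 120)/80 = 67.5 min, although no duration that existed in both arms has changed.

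**Episiotomy in all randomised women.** Count caesarean as none and assume a 30% rate among vaginal births in both arms. Caesarean rates of 25% and 20% give 0.30 × 0.75 = 22.5% against 0.30 × 0.80 = 24.0%. Rates of 25% and 15% give 22.5% against 0.30 × 0.85 = 25.5%. This is a valid randomised comparison, but any effect on mode of birth feeds into it, so it must be read beside mode of birth.

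**The case against.** **Episiotomy and tears.** A reader might infer that these, too, cannot be compared between randomised groups. The plan does not support that. It sets no vaginal-birth denominator for them, and a caesarean without episiotomy or tear can be recorded as none, so every randomised woman has a value. The problem arises only if the analysts restrict to vaginal births.

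**A reversal of direction.** A reader might also infer that conditional and randomised analyses of episiotomy would point opposite ways. Extend the round-number example with 21 episiotomies among the 70 control vaginal births and 8 more among the ten converted births. Among vaginal births the rate goes from 21/70 = 30% to 29/80 = 36%; in all randomised women it goes from 21% to 29%. Both rise. Only a different endpoint, vaginal birth without episiotomy, moves the other way, from 49% to 51%. That reflects the choice of endpoint and does not demonstrate selection bias.

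**The Background.** It would be too strong to say that the Background expects PFME to change mode of birth. It says potentially, calls the evidence mixed and states no effect on caesarean. If there is none, the bias is zero.

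**Detail for the analysis plan.** Denominators are commonly fixed in a fuller document that is not shown, and their absence is not held against the article. The article also promises to report missing data with reasons, and mode of birth will be compared by arm anyway. What remains is that the article commits stage durations to an analysis they cannot receive. Reporting reasons for missingness does not repair that, because these values never existed.

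**Conclusion.** The point holds for stage-of-labour durations, above all the second stage. The promised intention-to-treat t tests cannot include all randomised women, and the comparison that remains is conditional on an outcome PFME may affect. For episiotomy and perineal trauma it holds only if they are analysed among vaginal births alone.

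The size is modest: no bias if mode of birth is unaffected, and about 0.02 to 0.10 SD with a false-positive rate of about 5% to 12% if caesarean rates differ by 5 to 10 points. Those figures rest on assumed caesarean rates, an assumed correlation of 0.3 to 0.7, a simple threshold model and 100 women per arm with birth data. These are secondary outcomes and the primary analysis is unaffected. The correction is still worth making, because it changes what may be claimed about PFME and the course of labour.

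**What to change.** State in the analysis plan:

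1. Mode of birth is analysed in all randomised women and presented first among the childbirth outcomes.
2. Episiotomy and perineal trauma are analysed in all randomised women, with a caesarean without episiotomy or tear counted as none, and are interpreted beside mode of birth.
3. Stage durations, and any rates among vaginal births only, are reported as conditional and descriptive, with the number contributing per arm and no claim of a randomised effect.

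Composites such as vaginal birth without episiotomy may be added as supplementary endpoints. They should not replace the listed ones: counting every caesarean as a failure is a value judgement, it lets mode of birth drive the perineal result, and recruitment has already begun.

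The cost is a few sentences, since the data already come from the hospital database. The small downside is that no confirmatory claim can be made on stage durations.
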